### 7. Statistical analysis

#### 7.1. Sample size

The data used for the power calculation of the inhibition function primary outcome measures are from a sample of 175 ADHD individuals assessed off and then on stimulant medication (methylphenidate or dexamphetamine; data not published). The power calculation of the emotional function primary outcome measures are based on a sample of 30 ADHD participants from the same sample.

Power was set at 0.9, alpha level at 0.05, and the mean difference (change in off-versus on-medication) and standard deviations for the mean of the n = 175 group was used. The means for the n = 30 group were set at '0', since there was no change expected in these outcome measures for the placebo group. After applying the pilot data means from each primary outcome measure the highest sample size estimate we obtained was n = 152 for each group under two-tailed conditions. Therefore, a minimum total of 152 participants are required in this cross-over study to achieve the desired level of probability in detecting a statistically significant difference across the two primary outcome measures.

#### 7.2. Data upload and reports

A computerized protocol will quantify cognitive data in a standardized manner. Responses obtained from the questionnaires will be paper-based, and entered into computer-based scoring spreadsheets which have been set up to automatically score each questionnaire. Raw and composite IntegNeuro™ data for all sites will be extracted and stored by the Brain Resource Company Ltd., which will be periodically forwarded to the Sydney site (once per month).

IntegNeuro™reports (from Brain Resource Company Ltd.) will be generated and sent to the referring study clinicians after Session 1 and Session 3 testing. These reports will present performance at Session 1 compared to normative data, and after Session 3 (comparing performance after Session 2 and Session 3, including comparisons to normative data).

#### 7.3. Data analysis

The ACTION study will adopt an all available data analytical approach, meaning that all data obtained will be included in analyses, regardless of adherence to the study. Accordingly, there will be no imputation of missing data. For all analyses, a *p *value of <0.05 will be considered statistically significant.

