## Methods/Design

### 1. Study regimens

Eligible and consenting participants will complete rating scales and a computer-based test battery to assess cognitive performance. Figure 1 shows the schema for the ACTION study, which is a randomized double-blind cross-over study. After baseline assessment, participants will be randomized to receive either ATMX (brand name: Strattera) or placebo (starch powder with silicone 5% in a gelatin capsule) first, for six weeks (Phase A), before undergoing a one-week "washout" period (no capsules). Cross-over will occur after this washout period, and participants will receive the other compound (i.e., the compound they did not receive during Phase A) over a second six-week period (Phase B). Baseline (Session 1) assessments will be repeated at all time-points. ATMX doses will be based on the participant's weight, according to five pre-determined weight groups, covering the predicted weight ranges from 18 to 80 kg (Figure 2). Both the ATMX and the placebo capsules will look identical, and were purchased from Eli Lilly Australia.

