### 2. Participant study visits

#### 2.1. Screening (pre-Baseline)

Potentially eligible patients will undergo a clinical examination by a participating clinician. A primary diagnosis of ADHD will be based on *Diagnostic and Statistical Manual of Mental Disorders - Fourth edition *criteria [35]. The ADHD-RS IV will be used to confirm ADHD diagnosis, ADHD subtype, and to assess symptom severity. Additionally, the Anxiety Disorders Interview Schedule for Children (ADISC) [36] will be used to assess the presence of comorbid conditions. The ADHD-RS IV and ADISC scales are detailed in Section 4. They have been shown to have excellent reliability [36], validity [37], and medium-to-high specificity and sensitivity [38] in children and adolescents. The purpose of the Screening visit will be to confirm a primary diagnosis of ADHD, to determine symptom ratings, and eligibility for the study, as determined by participating clinicians.

Participants deemed eligible for the ACTION study will undergo a two-week washout period prior to Baseline testing (Session 1) if they are taking any ADHD medication at the time of Screening. Subsequent visits occur at weeks six and 13. Appointments will be confirmed over the telephone at least one day prior.

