##### 7.3.3. Post treatment

Repeated measures analysis of variance (ANOVA) will be performed on continuous variables (see Section 5), comparing the results obtained between baseline and ATMX, baseline and Placebo, and between ATMX and Placebo. Cohen's d effect size will be calculated using the mean differences between baseline and ATMX, and baseline and Placebo. Analyses will be performed in the total cohort, and then comparing those with and without comorbid anxiety. Presence/absence of previous stimulant treatment for ADHD, and an interaction term between presence/absence of comorbid anxiety and previous stimulant treatment will be used as covariates.

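### The named repeated-measures ANOVA makes the atomoxetine-placebo comparison a complete-pairs analysis, although Section 7.3 promises that all obtained data are used without imputation

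*Protocol article*

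**What the plan says.** Section 7.3 sets the analysis policy: "all data obtained will be included in analyses, regardless of adherence to the study". It continues: "Accordingly, there will be no imputation of missing data".

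Section 7.3.3 sets the method: "Repeated measures analysis of variance (ANOVA) will be performed on continuous variables", "comparing the results obtained between baseline and ATMX, baseline and Placebo, and between ATMX and Placebo". Cohen's d is to be computed from the two baseline contrasts, baseline to atomoxetine and baseline to placebo.

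The design gives one assessment per treatment. After baseline, "Subsequent visits occur at weeks six and 13" (Section 2.1). Session 2 follows Phase A and Session 3 follows Phase B, in which the child takes the compound not taken in Phase A (Section 1). The article names no mixed or other likelihood-based model and gives no rule for children with only one treatment assessment.

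**The concern.** Classical repeated-measures ANOVA needs every level of the within-child factor for each child it uses. With imputation ruled out, a child who leaves during the washout or Phase B has no value for one of the two treatments and cannot enter their comparison. That comparison is the only one protected by randomisation, and it would rest on children with both Session 2 and Session 3.

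If the decision to leave depends on how Phase A went, the remaining pairs are a selected group and the estimate can shift. The report could still describe the result as an all-available-data analysis, and a reader would not know that the contrast used complete pairs only.

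**Working it through.** **1. Who enters which comparison**

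| Child | Observed | One three-level ANOVA | Baseline-atomoxetine pair | Baseline-placebo pair | Atomoxetine-placebo pair |
|---|---|---|---|---|---|
| Attends all sessions, adherent or not | all three | yes | yes | yes | yes |
| Atomoxetine-first, leaves after Session 2 | baseline, atomoxetine | no | yes | no | no |
| Placebo-first, leaves after Session 2 | baseline, placebo | no | no | yes | no |

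The last column is the same whichever way the ANOVA is run. On the pairwise reading, the two baseline contrasts, and the Cohen's d values taken from them, come from different sets of children. As a practical check, a standard repeated-measures ANOVA routine given one child without the third value refused to run because the data were unbalanced.

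**2. The plan's own figure**

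Section 7.1 gives 152 at power 0.90 and two-sided alpha 0.05. The pilot mean difference and SD are not printed, so 152 cannot be reproduced. Solving backwards with 1.960 + 1.282 = 3.242:

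- if 152 is the number of pairs, dz = 3.242/√152 = 0.263;
- if 152 is per group in a two-sample formula, d = √2 × 3.242/√152 = 0.372.

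Power among n complete pairs is Φ(dz√n − 1.960). At 20% loss n = 121:

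- with dz = 0.263, power is Φ(0.263 × 11 − 1.960) = 0.82;
- with d = 0.372, dz = d/√(2(1 − ρ)), and power is 0.93, 0.98 and above 0.99 for within-child correlation ρ = 0.3, 0.5 and 0.7.

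**3. Bias under assumed dropout**

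Dropout rate, mechanism and ρ are assumptions, because the article gives none of them. Common settings: 152 children, 1:1 sequences, outcome SD 1, lower scores better, no period effect, ρ = 0.5 or 0.7.

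*First set: true difference −0.372, 1,500 runs per setting.* Dropout is random or rises with a poor Session 2 score. The complete-pairs estimate averages the two sequence means (period-adjusted). The comparator is a generalised least squares estimate using every observed value.

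| Mechanism | Complete pairs | All observed values |
|---|---|---|
| Completely random, 10-30% | −0.370 to −0.377 | −0.370 to −0.377 |
| Session 2 score, both sequences | −0.341 to −0.364 | −0.370 to −0.375 |
| Session 2 score, atomoxetine-first only | −0.403 to −0.498 | −0.369 to −0.375 |

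Bias in row 2 runs from 0.372 − 0.364 = 0.008 to 0.372 − 0.341 = 0.031 SD towards the null. In row 3 it runs from 0.403 − 0.372 = 0.031 to 0.498 − 0.372 = 0.126 SD away from it. Without period adjustment the ranges are about 0.01-0.02 and 0.03-0.10 SD. Evaluating the assumed dropout function, row 2 corresponds to losing about 10, 20 or 30% of placebo-first and 6, 12 or 20% of atomoxetine-first children. Row 3 corresponds to losing about 10, 21 or 33% of atomoxetine-first children, so its upper end needs a third of that sequence to leave. Under random dropout the all-data standard error is about 1-9% smaller (for example 0.0966/0.0883 = 1.09 at 30% loss, ρ = 0.5).

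*Second set: true difference −0.30.* Atomoxetine-first children leave at random; the placebo-first children with the worst change from baseline leave.

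| Loss, atomoxetine-first / placebo-first | ρ = 0.5 | ρ = 0.7 |
|---|---|---|
| 10% / 20% | −0.22 to −0.23 | −0.24 to −0.25 |
| 15% / 25% | −0.20 to −0.21 | −0.22 to −0.24 |

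Each range covers separate simulations. Bias is 0.05-0.10 SD towards the null. The children lost number 76 × 0.10 + 76 × 0.20 = 22.8, or 76 × 0.15 + 76 × 0.25 = 30.4. Applying the same worst-change rule to both sequences at an equal 15% leaves essentially no bias (about −0.30). Applying it to atomoxetine-first only, at 10%/20% and ρ = 0.5, gives −0.35.

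**The case against.** The policy sentence can be read as an ordinary available-case rule: non-adherent children are kept, gaps are not filled, and each analysis uses whoever has the data it needs. Section 7.3.3 lists three two-way comparisons, so a child who leaves after Session 2 still contributes to one of them, and an atomoxetine-first leaver can also enter the response models of Section 7.3.2. The article is a condensation, and handling of incomplete pairs is often settled in an analysis plan.

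Much of this stands, and it rules out several stronger statements that a reader might infer:

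- *Every child who leaves is deleted from the analysis.* This is true only if one three-level ANOVA is fitted, and the article does not say that it will be.
- *This is a per-protocol analysis.* It is not: non-adherent children who attend both sessions stay in.
- *The treatment effect will be diluted by about a quarter.* That size, (0.30 − 0.229)/0.30 = 24%, belongs to one assumed mechanism. Others give no bias or inflation.
- *The trial loses its power.* That depends on what 152 means, which the article leaves unclear. On the two-sample reading, power at 20% loss remains at least 0.93 for the correlations tried.

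The objection does not remove the core. On any reading, ANOVA without imputation excludes these children from the randomised contrast, and the article does not say so. That follows from a method the article names, not from detail left to another document.

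**Conclusion.** The concern holds in a limited form. The all-data policy in Section 7.3 is not met for the atomoxetine-placebo contrast by the method in Section 7.3.3, which yields a complete-pairs result. Neither the size nor the direction of any bias can be fixed from the article. Under the assumed scenarios it ranges from nil (completely random dropout, with a small loss of precision), through about 0.01-0.03 SD towards the null (Session 2 score-dependent dropout in both sequences) and up to about 0.1 SD towards the null (poor responders leaving placebo-first only), to about 0.03-0.13 SD away from the null (response-dependent dropout in atomoxetine-first only). Selection is the main risk and precision a lesser one. The all-data estimate stayed on target throughout the first set, but dropout there was either random or dependent on observed scores, which is the condition under which such an analysis is valid.

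**What to change.** In Section 7.3.3, make the primary analysis of the continuous endpoints a linear mixed model fitted by likelihood to every attended session, with fixed effects for treatment and session (period), sequence if wanted, the covariates already planned, and a random child effect. Take atomoxetine minus placebo from that model. Children with only Sessions 1 and 2 then contribute without imputation, and the sentence in Section 7.3 becomes true. Keep the repeated-measures ANOVA as a sensitivity analysis, labelled as complete pairs.

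The cost is analysis wording only: no new data, visits or participants. The small downside is that the model relies on data being missing at random given the observed scores, which should be stated.

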##### 7.3.1. Baseline analyses

Continuous data at baseline will be checked for normality of distribution and log-transformed if required. Logistic regression models will be used to determine whether or not the cognitive and emotion measures (using the composite scores) predict the presence of comorbid anxiety (as determined using the ADISC questionnaire).

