#### 1.2. Study participants

Figure 3 lists the inclusion and exclusion criteria for the ACTION study. Eligibility criteria include normal body mass for age and gender [34], age of 6 to 17 years (inclusive), and a primary diagnosis of ADHD. Both boys and girls will be enrolled into the study. The presence of any of the exclusion criteria listed in Figure 3 will preclude the participant from enrolling into ACTION.

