#### 4.4. IntegNeuro™battery

The IntegNeuro™ cognitive test battery is made up of 13 different tasks which require a total of approximately 50 minutes to complete. The 13 tasks which make up the IntegNeuro™ test battery were designed and validated to challenge participants in six different cognitive domains: i) Sensori-motor; ii) Learning and memory; iii) Language; iv) Attention and working memory; v) Executive function/planning; and vi) Emotion identification [1,31,32]. Table 1 lists the specific markers which will be investigated in ACTION for cognitive and emotional function and the tasks and measures used in IntegNeuro™ to ascertain them. Each marker is a composite of up to three tasks, and have a combined sensitivity of 88% in children and adolescents with ADHD [1]. The decision to focus on the Inhibition and Emotion identification markers as primary outcomes for the ACTION study was due to recent investigations [42,51], which led us to hypothesize that these markers would be more likely to improve after non-stimulant treatment in patients with ADHD and comorbid anxiety. Research into the cognitive markers in ADHD and their response to different ADHD treatments is still in the early stages so it would be premature to limit our investigations to only two of six markers which have been validated in ADHD. Hence, all six markers will be assessed in ACTION due to the novelty of this study. Marker scores are the focal dependent measures of interest, calculated as standardized scores for the tasks each marker comprises (Table 1). More detailed scores for each individual task will also be available for secondary analyses. Williams et al. (2010) provides a clear description of the tasks which will be used in ACTION [1].

**Table 1 T1:** Six cognitive and emotional function markers, and their contributing measures

Marker	Summary definition	Task	Measure
Cognitive:			

1. Sustained attention (vigilance)	To maintain attention over time during continuous and repetitive activities.	Continuous performance task	Reaction time, total errors

2. Impulsivity	To initiate a behavior without adequate forethought; the inability to suppress automatic responses when they are inappropriate.	Continuous performance task Go-NoGo	Errors of commission Errors of commission

3. Intrusions	The repetition of erroneous responses, even in the absence of interfering stimuli.	Maze Switching of attention Verbal memory recall	Overrun errors Errors (digits and letters) Total intrusion errors

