### 5. Research endpoints

The primary endpoint will be clinically significant improvement in cognition and emotional function after ATMX treatment assessed using IntegNeuro™ (Table 1); and in ADHD symptoms (ADHD-RS IV, CGI, WPREMB, and CPRS-R subscales: Cognitive problems/inattention, Hyperactivity, Conners' ADHD index, CGI restless-impulsive, CGI total, DSM-IV inattentive, DSM-IV hyperactive-impulsive, and DSM-IV total). Further analyses will be undertaken to compare the differences in ATMX treatment effects between participants with and without comorbid anxiety; and between ADHD subtypes.

Part of the novelty of this trial lies in our utilization of objective assessments for cognition and emotional function. As such, we will also determine if our objective measures predict response to ATMX in ADHD, and in patients with comorbid anxiety. Treatment response is defined in Section 7.3.2.

The secondary endpoints will be improvements after ATMX treatment in quality of life (PedsQL - self and parent); emotional states and self-regulation (DASS-BRISC); and state and trait anxiety (CPRS-R subscales: Anxious-shy, STAI and STAIC). Previous ADHD treatment with stimulant medication and comorbid anxiety will be included as covariates.

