##### 7.3.2. Predictors and moderators of response to treatment

Simple linear regression models will be used to observe any relationships between cognition/emotion composite scores at baseline and questionnaire scores after ATMX treatment to see if the objectively-measured cognition/emotion measures are related to the subjectively-measured ADHD symptom measures (ADHD-RS IV, CPRS-R). To examine the *predictive *relationship of cognition/emotion measures on ADHD symptom measures, changes after ATMX treatment in ADHD symptom measures will be categorized depending on whether or not they responded to the treatment. Analyses will be performed using two different definitions of treatment response: 1) ≥25% improvement and 2) ≥40% improvement; while non-response will be defined as 3) <25% improvement and 4) <40% improvement [11,17,19,52]. More specifically regarding the primary outcome, six predictors (the composite scores from baseline for the six cognition and emotional function markers, Table 1) will be used in logistic regression models to examine if baseline performance in these measures predict response to ATMX. Response in terms of the primary outcome will be defined initially as a ≥25% improvement (versus <25% improvement) in ADHD-RS IV and CPRS-R t scores (see Section 5). A secondary, more stringent definition of response will subsequently be implemented, using a response cut-point of ≥40%. With a planned sample size of >60, these analyses will be sufficiently powered. Further exploratory analyses may be performed at a later date.

Absolute change scores (continuous ADHD symptom data) will be used to see if the cognition/emotion measures *moderate *response to ATMX in ADHD symptom measures. These investigations will initially be performed on the total ADHD cohort, before examining any differences between those with and without comorbid anxiety.

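### The between-child marker models carry no age term and the reference for the standardized marker scores is not stated, so if those scores still reflect age, a marker that only tracks age could be reported as related to anxiety or to symptoms after atomoxetine

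*Protocol article*

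**What the plan says.** The protocol article sets out three kinds of model that compare one child with another.

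- **Comorbid anxiety (7.3.1).** Logistic regression is to "determine whether or not the cognitive and emotion measures (using the composite scores) predict the presence of comorbid anxiety". No other term is named.
- **Symptoms after atomoxetine (7.3.2).** "Simple linear regression models will be used to observe any relationships between cognition/emotion composite scores at baseline and questionnaire scores after ATMX treatment". A simple linear regression has one predictor.
- **Response to atomoxetine (7.3.2).** "six predictors (the composite scores from baseline for the six cognition and emotional function markers, Table 1) will be used in logistic regression models". All six places are taken by markers. Response means at least 25%, then at least 40%, improvement. Absolute change scores are used for moderation.

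Section 1.2 sets the age range at 6 to 17 years. Section 4.4 describes the markers as "calculated as standardized scores for the tasks each marker comprises" and does not name the reference population. Section 7.2 mentions norms only for the clinicians' reports: "These reports will present performance at Session 1 compared to normative data". Section 4.1 takes the ADHD-RS IV as a total score.

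Covariates are named in two places. The paragraph on secondary endpoints in section 5 ends: "Previous ADHD treatment with stimulant medication and comorbid anxiety will be included as covariates". Section 7.3.3 names previous stimulant treatment and its interaction with anxiety for the repeated-measures ANOVA. Age is in neither list.

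**The concern.** Table 1 builds the markers from error counts, reaction times, reaction-time variability and percentage correct, in children whose ages span twelve year-groups. Performance of this kind may well change with age. In the atomoxetine-placebo contrast each child is his or her own control, so age drops out. In the models above, children are compared with one another, and the cross-over gives no such protection.

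If a marker and an outcome both move with age, a model without age credits the marker with what age explains. The Background says the trial should show which objective markers relate to atomoxetine response, in support of individual treatment decisions. A clinician already knows the child's age, so a 50-minute battery is useful for what it adds to that. As specified, the models cannot separate the two.

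**Working it through.** **The plan's own figure.** Section 7.1 gives 152, but no mean difference or SD, so it cannot be reproduced. With power 0.9 and two-sided alpha 0.05 it corresponds to a standardized difference of (1.960 + 1.282) × √(2/152) = 0.372 for two groups of 152, or (1.960 + 1.282)/√152 = 0.263 for 152 pairs. The present point does not depend on it; 152 is used only as the number of children.

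**Inputs from the article.** Ages 6 to 17; p<0.05 for all analyses (7.3); N = 152 (7.1) and, as a lower case, N = 60, because 7.3.2 speaks of more than 60.

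**Assumptions, none of them in the article.** Marker-age correlation 0 to 0.7; odds ratio for anxiety per SD of age 1.0, 1.5 or 2.0; age-symptom correlation 0, 0.2 or 0.3; anxiety prevalence about 40%.

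**Model.** Age is uniform from 6 to just under 18, with a = (age − 12)/√12.

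- Marker = r·a + √(1 − r²)·noise
- logit P(anxiety) = ln(0.4/0.6) + ln(OR)·a
- Symptom score = q·a + √(1 − q²)·noise

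Given age, the marker is unrelated to either outcome. Each setting was simulated 1,500 times, with one marker, and the share of trials with marker p<0.05 was counted. The Monte Carlo standard error is √(0.05 × 0.95/1500) = 0.6 percentage points near 5% and at most 1.3 points.

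**Results at N = 152, marker p<0.05:**

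| Marker-age r | Age-outcome link | Logistic, no age | Linear, no age | Logistic, with age | Linear, with age |
|---|---|---|---|---|---|
| 0 | OR 2.0; q 0.3 | 4.6% | 5.1% | 4.6% | 4.5% |
| 0.5 | none | 4.8% | 5.5% | 4.7% | 5.7% |
| 0.3 | OR 1.5; q 0.2 | 12.2% | 12.7% | 4.3% | 6.1% |
| 0.3 | OR 2.0; q 0.3 | 20.0% | 19.1% | 5.7% | 4.0% |
| 0.5 | OR 1.5; q 0.2 | 21.9% | 24.2% | 5.9% | 5.7% |
| 0.5 | OR 2.0; q 0.3 | 49.5% | 44.7% | 5.0% | 6.2% |

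At r = 0.7 the rates without age reach 37% to 79%. At N = 60, over r = 0.3 to 0.7 with an age-outcome link, they run from 7% to 39%. With age in the model they stay at about 4% to 6% throughout.

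**Hand check of the linear column.** Without age, the marker-symptom correlation is r × q. By Fisher's transformation the rejection rate is Φ(λ − 1.96) + Φ(−λ − 1.96), with λ = atanh(rq)·√(N − 3).

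- r = 0.3, q = 0.2: rq = 0.06, λ = 0.733, rate 11.4% (simulated 12.7%)
- r = 0.5, q = 0.3: rq = 0.15, λ = 1.845, rate 45.4% (simulated 44.7%)

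The product rq also shows why both links are needed: if either is zero, nothing is left to inflate.

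**Cost in the response model.** Taking the Background's response rate of up to 63.5% as an assumption, 60 children give 60 × 0.365 = 21.9 non-responders. That is 3.65 per predictor with six predictors and 3.13 with seven.

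**The case against.** The strongest reply is that the decisive premise is open. Standardized may mean standardized to age norms: section 7.2 shows that norms for the battery exist, and a condensed article may leave the scoring reference to the full protocol or the cited validation work. If so, the marker-age correlation is near zero and the check shows no inflation. This stands, and it makes the point conditional. It does not remove it, because Table 1 mixes units such as errors and reaction times, so the word may equally mean no more than rescaling to a common unit.

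A reader might infer from the covariate lists in section 5 and section 7.3.3 that age was deliberately excluded from every model. The text does not support that. The first list closes the secondary-endpoint paragraph and the second belongs to the ANOVA; neither governs 7.3.1 or 7.3.2. The omission rests on the wording of those two sections alone. That wording is firm in 7.3.2 and looser in 7.3.1, which names the composites without closing the list.

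It can also be said that an association running through age is a real association, so a significant result is not false for the question as worded. That is correct for bare prediction. The rates above count markers that add nothing beyond age, which is the more useful question for the stated purpose.

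Finally, percentage response and absolute change are measured against the child's own baseline, so stable age differences in symptom level partly cancel. No age link to these outcomes is shown in the article, and the check did not cover them.

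**Conclusion.** The point holds as a conditional one. The text establishes that none of the models in 7.3.1 and 7.3.2 names age, in a sample aged 6 to 17, and that the reference for the standardized markers is not stated. Whether this biases anything depends on two facts the article does not give: whether the analysed scores still vary with age, and whether anxiety status or ADHD-RS IV totals do.

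If both are true to the assumed degree (marker-age correlation 0.3 to 0.5, moderate to strong age-outcome link), a marker with no association given age is significant in about 12% to 50% of trials of 152 children, against about 5% after adjustment. If either is false, there is no inflation.

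The case is best for the anxiety model and for post-atomoxetine ADHD-RS IV totals. It is weaker for the CPRS-R, which is recorded as T-scores, and unproven for response and absolute change. A reader might go further and conclude that the trial's treatment effect is confounded by age, or that its size is wrong. Neither follows: the atomoxetine-placebo comparison is within child, and the sample-size calculation does not use these models.

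**What to change.** 1. In section 4.4, state what the marker composites are standardized against, whether that reference is age-specific, and that the same one is used at all three sessions.
2. In section 7.3.1, add age at Session 1, as a continuous term, to the logistic model of comorbid anxiety.
3. In section 7.3.2, replace the simple linear regressions of post-atomoxetine questionnaire scores by models with the marker and continuous age, so that they show what the marker adds beyond age.
4. Report the response models (25% and 40% cut-points) and the absolute-change models with and without age, as a sensitivity analysis.

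An age-outcome link alone does not confound. If the composites prove to be fully age-normed, items 2 and 3 therefore change little and cost little.

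The change is to analysis wording only and needs no new data. It costs one degree of freedom per model. That matters most in the six-predictor logistic model if only slightly more than 60 children are analysed, which is why age enters there as a sensitivity analysis.
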